#### Progression criteria

Progression criteria for the trial will be considered in a holistic way with consideration given to possible refinements and adaptations that can be made to the intervention and the trial processes to mitigate any barriers encountered. Whilst we can set quantitative thresholds indicating success on elements of the feasibility trial, these will be taken into consideration with the context of the conditions under which these were obtained, in addition to qualitative information collected. Non-progression will only be considered on the basis as to whether any of the conditions are unlikely to be resolved. Quantitative criteria will be fixed on recruitment and retention, whilst trial processes, suitability of proposed outcome measures, acceptability and fidelity will be assessed by a qualitative approach understanding the context of these. Successful recruitment will be denoted as achieving greater than 75% of proposed sample; less than 25% recruited of the proposed sample will be defined as unsuccessful and unlikely to be remedied. Successful retention will be denoted as greater than 70% of the recruited sample with unsuccessful retention denoted as less than 20% of the recruited sample.

### Recruitment

Participants will be recruited from two sources:Caregivers who have already consented to be involved in the wider RDS Impact study [30]Caregivers who contact us following various communications about the study (e.g. via the RDS service newsletter and social media, discussions between RDS members and RDS workers).

The consent procedure is as follows: (1) participants should first consent to participate in the wider RDS Impact study [30] of which this educational programme is a sub study, (2) participants will be sent a link to a Qualtrics page (Qualtrics, Provo, UT), at which point they will access screening questions as to their suitability for inclusion, (3) if they are screened as eligible, they will be directed to an online opt-in consent form that they should complete before given access to the survey collecting demographics and baseline measures, and (4) if they are screened as ineligible, they will be directed to a page thanking them for their interest in the study and giving them email contacts for the Rare Dementia Support service in case they want to reach out for support. Both consent forms can be found in Appendix I. Using Qualtrics display logic, those who do not consent will automatically receive a message thanking them for considering involvement in the study and asking them why they chose not to participate (being clear that they do not have to answer this if they do not want to).

We will recruit from each diagnostic group as screened. Up to fifteen semi-structured interviews will explore the experience during the study of a subgroup of participants. Individuals will be purposively sampled (by diagnostic subtype and allocation group) and approached via email asking if they want to participate. Interviews will be conducted post follow-up via Zoom.

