### Study design

This is the protocol for a pilot randomised wait-list controlled feasibility trial followed by a qualitative evaluation (mixed-method study). Participants randomly allocated to the intervention group will receive access to the educational programme for 8 weeks. Those in the wait-list control group will receive treatment as usual (i.e. pointed to Rare Dementia Support website (https://www.raredementiasupport.org/)) and access to the programme at the end of data collection. The wait-list aimed to decrease attrition and also meet ethical demands (e.g. giving caregivers access to tailored educational resources that may potentially have a beneficial effect). Outcome measures will be collected at baseline, 8-week and 3-month post-randomisation. Semi-structured interviews will be conducted after completion of the 3-month follow-up baseline measures as part of a process evaluation. The study participant flow chart is shown in Fig. 1.

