### Power calculation

As this is a feasibility study, a formal power calculation is not required; however, the sample size does require justification. This study was initially intended to develop a tool for carers of people with bvFTD only. However, during the interviews with stakeholders, became apparent the need and opportunity to develop two more tools, to cover PPA and PCA (details of sample calculation for bvFTD only can be found in Brotherhood et al., [31]. Originally, we aimed to recruit 135 participants comprising 45 caregivers from each of the three diagnostic groups that the intervention is designed for (PCA, PPA, bvFTD) with a 30:15 intervention control split in a 2:1 randomisation. This would have provided both a precise estimation of the overall retention rate but also within diagnostic group. Reviewing this target once recruitment was underway, we acknowledged that this would be a large feasibility study, and with a rarer disease, it would require recruiting a large proportion of the available population. Therefore, we revised the target sample down to 30 participants (randomised 20:10 in favour of the intervention); this would allow an understanding of the trial processes, allow for adaptation and refinement of the intervention and understand acceptability and fidelity within the population. The confidence intervals on our estimates will be wider, but this is an acceptable concession given the sparsity of the potential population to recruit. We will achieve a 95% confidence interval of ±18.7% around our expected value of 76% of those completing the intervention and pre-post measures whilst viewing 70+% sessions. In terms of retention to the study, we will achieve a 95% confidence interval of ±15.5% around our expected value of 75%.

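### Neither the interviews nor the follow-up questionnaire provide for withdrawers or non-responders, so the retrospective acceptability evidence used for progression is likely to be weighted towards retained participants

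*Protocol article*

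**What the plan says.** Retrospective acceptability is part of the primary objective (Aims and objectives). The section on acceptability measures gives it two sources: a brief questionnaire, intended to reach all participants and included in the follow-up measures, and in-depth interviews with about 15 people.

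On the interviews, Recruitment states: "Up to fifteen semi-structured interviews will explore the experience during the study of a subgroup of participants". Its sampling rule is: "Individuals will be purposively sampled (by diagnostic subtype and allocation group) and approached via email asking if they want to participate". On timing, Recruitment states: "Interviews will be conducted post follow-up via Zoom". Study design is more specific: "Semi-structured interviews will be conducted after completion of the 3-month follow-up baseline measures as part of a process evaluation". I read this as the 3-month follow-up measures.

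Progression criteria sets numeric thresholds for recruitment and retention only. For the rest it says: "suitability of proposed outcome measures, acceptability and fidelity will be assessed by a qualitative approach understanding the context of these".

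Three other provisions bear on people who leave or disengage:
- Feasibility measures plans to report withdrawals and non-respondents, with timing and with reasons where these apply.
- Prospective acceptability includes reasons for discontinuing.
- Concurrent acceptability uses task completion and the number of contacts with the facilitator.

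**The concern.** People who withdraw, stop answering or barely use the programme are the ones best placed to say what was unacceptable about it or about the trial. Both retrospective sources depend on reaching the follow-up surveys or the period after them. The interview sampling rule names diagnosis and arm and nothing on engagement.

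This bears on the decision the pilot exists to inform. Under Progression criteria, the full trial is put in doubt only if a problem looks unlikely to be resolved. Judging that requires knowing why people left or stopped, not only how many did. The Qualitative data section also has saturation assessed as the interviews proceed, so saturation could be declared without hearing from anyone who left.

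**Working it through.** **Inputs (Power calculation, Progression criteria, Recruitment).** Sample 30, randomised 20:10. Expected retention 75%. Expected completion of intervention and measures 76%. Retention counts as successful above 70%. At most 15 interviews.

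**1. The plan's own figures.** The half-width is 1.96 × √(p(1 − p)/n).
- Retention: 1.96 × √(0.75 × 0.25/30) = 15.5%. This matches the statement "we will achieve a 95% confidence interval of ±15.5% around our expected value of 75" per cent, so retention refers to all 30.
- Completion: 1.96 × √(0.76 × 0.24/20) = 18.7%, as stated, so completion refers to the 20 in the intervention arm.

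**2. Expected losses.**
- Overall: 30 × 0.25 = 7.5.
- By arm, assuming equal loss: 20 × 0.25 = 5 intervention and 10 × 0.25 = 2.5 control.
- Intervention participants not meeting the completion definition: 20 × 0.24 = 4.8. That definition combines programme use and pre-post measures, so these people overlap with the 5 lost and must not be added to them.
- If the true loss is 25%, the binomial probability that at least 5 of 30 are lost is 0.902.

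**3. What successful retention allows.** 21/30 is exactly 70% and does not exceed the threshold; 22/30 = 73.3% does. Up to 8 participants can be lost with retention still rated successful, and all 15 interviews can then come from the 22 retained.

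**4. Leavers among the interviewees.** Fifteen interviews spread in proportion to the sample would include 15 × 0.25 = 3.75 leavers. On the Study design wording the number is zero. On a looser reading it is unspecified.

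**5. Leavers who contribute to neither retrospective source.** The article does not say at which time point the 75% applies. Assume the questionnaire is given at both follow-ups, that no leaver is interviewed, and that a share f of losses occurs before the 8-week survey. The number is then 7.5 × f: 7.5 if f = 1, 3.75 if f = 0.5, and 0 if f = 0.

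**6. The sources side by side.**

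| Source | Covers those who leave or disengage? | Explains why in depth? |
|---|---|---|
| Interviews | Leavers not provided for; low users who answer the surveys eligible but not targeted | Yes |
| Follow-up questionnaire | Only those who answer a follow-up | Briefly |
| Withdrawal and discontinuation reasons | Yes, where a reason is given | Not described as in-depth |
| Task completion, facilitator contacts | Yes, intervention arm | No, counts only |

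The tasks follow modules 2, 3 and 4 only, and writing to the facilitator is encouraged rather than required (Intervention).

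**The case against.** The strongest reply is that the plan does collect acceptability evidence from these people. Discontinuation reasons are a named acceptability measure. Withdrawals and non-response are to be reported with timing and reasons where these apply. Task completion and facilitator contacts need no survey. Retention is itself a progression criterion, and the qualitative approach under Progression criteria is not confined to interviews. All of this stands. A reader might infer that the acceptability evidence as a whole leaves out those who withdraw or disengage; the documents do not support that.

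Three further points also stand:
- Someone who used the programme little but answered the surveys receives the questionnaire and can be interviewed. Such people are untargeted, not excluded.
- Someone lost between 8 weeks and 3 months may have answered the first follow-up questionnaire, so it cannot be said that all 7 or 8 leavers contribute nothing.
- The Recruitment wording can be read as timing alone. Exclusion of leavers rests on Study design, which does not expressly make completion a condition of invitation.

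It can also be argued that an article leaves the interview sampling matrix to the full protocol, and that a third stratum would be too fine. The first argument carries limited weight, because the article itself states the sampling factors and the timing. The second is right about a full stratum: 3 diagnoses × 2 arms × 3 engagement levels gives 18 cells for at most 15 interviews. It does not count against a looser sampling consideration.

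**Conclusion.** The point holds in a limited form. Followed as written, the in-depth interviews and the follow-up questionnaire make no provision for withdrawers or non-responders, and interviewees are not sampled by engagement. The retrospective acceptability evidence is therefore likely to be weighted towards retained participants. The other measures reduce the gap but do not close it, because they give little in-depth account of why people left or stopped.

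The size is about 7.5 of 30 participants, about 5 of them in the intervention arm. This rests on the plan's own 75% retention and on equal loss between arms. The number absent from both retrospective sources may be smaller, depending on when losses occur. The roughly 2.5 lost controls bear on trial processes but not on the programme, which they would not yet have received.

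It might be inferred that acceptability will be overestimated and barriers missed. That is the likely direction of the selection, but the documents do not establish it. The change is worth making because it serves a primary objective at little cost; the gap does not undermine the trial.

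**What to change.** Keep the maximum of 15 interviews and change the sampling and timing wording:
- Add engagement or withdrawal status as a sampling consideration beside diagnosis and arm, mainly in the intervention arm, and not as a full third stratum.
- Aim for a few interviews with withdrawn, non-responding or low-use participants. Proportional representation of leavers alone would be about 4 of 15.
- State that completing the 3-month measures is not a condition for invitation, and align Study design with Recruitment on this.
- Invite those who withdraw at the time of withdrawal, subject to their consent to contact.
- When reporting, give the number of interviewees by engagement and withdrawal status, so that readers can see whom the acceptability findings represent.

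The sample size and the number of interviews do not change. Uptake among those who leave will be lower, and the target may not be met. Coverage of the six diagnosis-by-arm cells, now 15/6 = 2.5 interviews each on average, becomes slightly thinner or less even, although each leaver interviewed still belongs to one of those cells.

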### Randomisation

Randomisation will be provided via secure online platform hosted by NWORTH CTU, Bangor University. The randomisation procedure will be carried out by the project manager of the study ([name]). Once consent and baseline measures have been completed, the participant can be entered into the randomisation system. Randomisation will be stratified by diagnosis (bvFTD, PPA, PCA). A dynamic adaptive randomisation algorithm will be used to maintain the allocation ratio of 2:1 in favour of the intervention and the balance within stratification variables. We intend to use an unequal allocation ratio during this feasibility study due to there being more uncertainties about the interventional arm than the control arm. Development of the intervention and adjustment to the different diagnosis groups will benefit from providing more data from the feasibility study on the intervention arm specifically. The recruiting researcher will not be aware of allocations made; randomisation will be completed by a researcher independent of the other trial processes. Given the nature of this trial, participants are not blinded to group allocation. Researchers are not blinded to group allocation either, but this does not bias measure collection since measures are self-reported online. Due to the use of unequal allocation in this stage of the evaluation, it is not possible to keep analysts blind — however, given that no inferential statistics will be generated, the risk for introduction of bias at this level is minimal. The trial will be subject to internal audit and monitoring from within NWORTH CTU. Additional regular biweekly meetings of the researchers will be conducted to monitor progress and discuss any arising issues. The whole trial will be overseen by the wider research group.

### Intervention

The intervention group will receive the Better Living with Non-memory-led Dementia programme, an 8-week duration 6-module educational programme covering the following topics: (1) welcome to the programme and what to expect from it, (2) understanding the disease, (3) how to provide better support for the person with dementia, (4) how to look after the caregiver’s own mental health, (5) where to find additional sources of support and (6) an introduction to the value of support groups. At the end of modules 2, 3 and 4, participants will be asked to complete a real-life task to put in practice skills learned in the specific module (e.g. approaching a friend and explaining the disease in lay terms). After that, every participant will be encouraged to reflect on that experience and share it with a programme facilitator via email. The facilitator will be a member of the team, with no clinical training, who will interact with the participant via email sticking to principles of active engagement (a script has been developed on this purpose based on principles of active listening adapted to written communication (see Appendix II). The facilitator will not act as an advisor as to the use of therapeutic techniques. All course modules will be printable using the PDF download button on the course’s page. An online version of the template for interventions description and replication (TIDIER) [32] checklist for this intervention can be found at tidierguide.org/#/gen/P2-xFB4ZH.

#### Intervention development

This educational programme was developed following the MRC guidance for development of complex interventions [25, 26, 33] comprising the following stages:

##### Stage 1: Identifying existing evidence and interventions

The initial idea about the development of this educational programme was prompted by the experience of the research team (consisting of academics, clinicians and support workers specialised in non-memory led dementias) interacting with people with PCA, PPA and bvFTD and their families over the years. Rare Dementia Support, a specialised national support service for these types of dementia, is run by our group at UCL. In this first stage of the development, the authors conducted a revision of the most up-to-date literature on the broad topic of provision of online support for caregivers of people with dementia, extracting information about relevant variables such as follows: intervention content, theories used for logic models, information about skills taught to caregivers in previous interventions, resources used to support learning, outcome measures, barriers and facilitators to caregiver engagement, details about how other blended interventions have been articulated, whether they work and if they are sustainable and have achieved successful implementation. A second step involved the revision of existing tools (both for online and face-to-face delivery). Since most online interventions fail to reach the implementation phase [34], it is not surprising that we found far more papers describing the efficacy of the tools than tools themselves which were available for the research team to test. The quality of the studies conducted also varied in quality. For the purpose to inform our intervention, we scrutinised a selection of studies that met the following criteria: (1) had a comparator group and (2) had a N above 20 in each arm (either RCT or pilot studies) [21, 35–49]. In a third step, we drew on the experience of colleagues leading the development of or administering online interventions. We therefore held a series of meeting during the evidence gathering phase. We met with research colleagues involved in the development of Communication Bridge [50], Partners in Balance [22] and Rhapsody [24], three tools recently developed or adapted for people with young onset and non-memory led dementias. Meetings with NHS clinicians working in memory services and IAPT services and experience in the use of digital tools were also held. Multiple websites offering online information, training, therapy and support were reviewed to inform web design, participant flow and user experience (e.g. https://www.dementiacarecentral.com, https://www.beatingtheblues.co.uk, https://www.partnerinbalans.nl/statics/de/).

##### Stage 2: Identifying theory

This educational programme is informed by theories of self-efficacy [51], behaviour change [52], coping theory [53] and social learning theory [51]. Self-efficacy is the person’s belief that one can perform competently and capably in given situation [51]. Caregivers with low self-efficacy beliefs tend to focus on their personal inefficiencies, the difficulty of the task and the negative consequences of failure. Self-efficacy is an important component of behaviour change. The COM-B model of behaviour change [52] argues that behaviour comes from an interaction of three factors: capability to perform the behaviour, opportunity and motivation to carry out the behaviour. Interventions for caregivers need to alter one or more of these three elements to achieve change. To select the most suitable behaviour change techniques (BCTs) for our intervention, we used the Theory and Techniques Tool [54] (https://theoryandtechniquetool.humanbehaviourchange.org/tool). This tool also provides potential links between the BCTs and mechanisms of action, which informed the format and content of the manuals of our programme. Coping refers to the strategies that individual use to manage stress [53], and these strategies may in turn affect the overall well-being of caregivers [55]. In the context of caregivers of people with dementia, coping strategies and social support can act as potential mediators between caregiver stressors and health outcomes [56]. Lastly, social learning theory [51] posits that people learn from each other from observing, modelling and imitating their behaviour. This latter theoretical framework influenced the format of the resources used in this educational programme (e.g. abundant vignettes and case studies, links to recordings of support group meetings and interviews with caregivers).

##### Stage 3: Modelling process and outcomes

Information from stages 1 and 2 was pulled together to develop a logic model (shown in Fig. 2). It was decided that the educational programme would consist of 6 modules or manuals following the structure of previous interventions for caregivers [22–24]. The broad content of the educational programme manuals was decided based on the intervention targets and the co-production work with people with lived experience described in the section below. The specific way to bring that content to life was shaped by the behaviour change techniques and mechanisms of action that were deemed to drive effective change and are listed in Fig. 2. According to our logic model, the outcomes of the educational programme are expected to include changes in caregiver self-efficacy, relationship with the care recipient, psychological status, quality of life and health and social health. The group of people with lived experience who co-produced the programme manuals also contributed to inform the clinical outcome measures used in the pilot feasibility trial.

**Fig. 2 Fig2:**
[figure not shown]
Logic model for the Better Living with Non-memory-led Dementia programme

